### Data collection on the day of transition to spontaneous ventilation

On the day of enrollment in the study, we will collect ventilatory parameters one hour before the transition to spontaneous ventilation and periodically during the first 24 hours of spontaneous ventilation. We will include patients who are transitioned and remain for at least one hour in one of the following ventilatory modes: pressure support ventilation (PSV), continuous positive airway pressure (CPAP), airway pressure release ventilation (APRV), neurally adjusted ventilatory assist (NAVA), proportional assist ventilation (PAV +) or adaptive ventilatory assist (AVA).

### One hour before transition

The following data on controlled ventilation will be recorded retrospectively: ventilatory mode; programmed respiratory rate; patient's total respiratory rate; minute ventilation; peak airway pressure; V_T_; and PEEP. We will also collect vital data (heart rate, mean arterial pressure, peripheral oxygen saturation), arterial blood gas analysis data (obtained as close as possible to the collection of ventilatory data will be recorded), the presence of major asynchronies,^(23)^ the use of vasopressors, the use of sedatives and analgesics, the RASS score, the presence of *delirium* assessed by the CAM-ICU scale or clinical assessment.

### One hour and every 6 hours until 24 hours after transition to spontaneous ventilation

Once the patient is included in the study, we will prospectively collect data at the end of the first hour and every six hours (with a tolerance of ± 1 hour) after the transition, including the ventilatory mode, patient's respiratory rate, minute ventilation, peak airway pressure, V_T_, PEEP, sensitivity setting, airway occlusion pressure at 100ms (P 0.1) and presence of asynchronies. We will also collect vital data, arterial blood gas analysis (if available), data on the use of vasopressors, data on the use of sedatives and analgesics, and data on sedation levels measured by the RASS and the presence of *delirium* (Table 3).

**Table 3 t3:** Data from the day of inclusion in the study

Variable	1 hour before	1 hour after	6 hours after	12 hours after	18 hours after	24 hours after
Tidal volume (mL/kg of PBW)	xx ± xx	xx ± xx	xx ± xx	xx ± xx	xx ± xx	xx ± xx
PEEP (cmH_2_O)	xx ± xx	xx ± xx	xx ± xx	xx ± xx	xx ± xx	xx ± xx
Respiratory rate (breaths/min)	xx ± xx	xx ± xx	xx ± xx	xx ± xx	xx ± xx	xx ± xx
Ppeak, (cmH_2_O)	xx ± xx	xx ± xx	xx ± xx	xx ± xx	xx ± xx	xx ± xx
Minute ventilation (liters/min)	xx ± xx	xx ± xx	xx ± xx	xx ± xx	xx ± xx	xx ± xx
FiO_2_	xx ± xx	xx ± xx	xx ± xx	xx ± xx	xx ± xx	xx ± xx
pH	xx ± xx	xx ± xx	xx ± xx	xx ± xx	xx ± xx	xx ± xx
PaO_2_ (mmHg)	xx ± xx	xx ± xx	xx ± xx	xx ± xx	xx ± xx	xx ± xx
SaO_2_	xx ± xx	xx ± xx	xx ± xx	xx ± xx	xx ± xx	xx ± xx
Heart rate (bpm)	xx ± xx	xx ± xx	xx ± xx	xx ± xx	xx ± xx	xx ± xx
Mean arterial pressure (mmHg)	xx ± xx	xx ± xx	xx ± xx	xx ± xx	xx ± xx	xx ± xx
RASS	x (x - x)	x (x - x)	x (x - x)	x (x - x)	x (x - x)	x (x - x)
*Delirium*	x (x)	x (x)	x (x)	x (x)	x (x)	x (x)
Asynchrony	x (x)	x (x)	x (x)	x (x)	x (x)	x (x)
Vasopressors	x (x)	x (x)	x (x)	x (x)	x (x)	x (x)

PBW - predicted body weight; PEEP - positive end-expiratory pressure; Ppeak - peak airway pressure; FiO_2_ - fraction of inspired oxygen; pH - potential of hydrogen; PaO_2_ - partial pressure of oxygen; SaO_2_ - oxygen saturation of arterial blood; RASS - Richmond Agitation and Sedation Scale. The data are expressed as the mean ± standard deviation, median (interquartile range) or n (%).

### Follow-up

We will follow patients until hospital discharge or death within the hospital and will compute the rate of adherence to low V_T_, that is, V_T_ ≤ 8mL/kg of PBW in the first 24 hours of ventilation in spontaneous ventilation, the proportion of patients with significant asynchrony in the transition to spontaneous MV, the proportion of patients returning for sedation and controlled MV in the first 24 hours, the proportion of patients returning to sedation and controlled MV at any time during MV, the rate of adherence to a low PEEP/FiO_2_ table in the first 24 hours, 28 day hospital survival and ventilator-free days. Ventilator-free days will be calculated as the number of days alive and out of MV to day 28. Patients who die before day 28 will be considered to have zero ventilator-free days; the day of inclusion will be considered day 0; for patients who are extubated and reintubated in the first 28 days, the number of ventilator-free days will be computed as the number of days alive and out of MV from the day of the last successful extubation (> 48 hours without MV) to day 28; for tracheostomized patients, the number of ventilator-free days will be computed as the number of days alive and out of MV from the day that the patient remains disconnected from the MV for more than six consecutive hours to day 28.

The data collection schedule is shown in figure 2 and table 1S (Supplementary Material).

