### Objectives and outcomes

The primary objectives are to estimate the prevalence of low V_T_ ventilation (V_T_ < 8mL/kg of PBW) in the first 24 hours of spontaneous ventilation in patients with hypoxemic ARF and its association with ventilator-free days on day 28. Tidal volume will be assessed five times over the first 24 hours after the transition to spontaneous ventilation to account for potential variation. To determine whether V_T_ was below or above 8 mL/kg of PBW for a given patient, we will calculate the weighted average V_T_ based on the duration of each evaluation period. Accordingly, the first assessment, collected one hour after the transition, carries a weight of 1/24, the second assessment, collected 5 hours after (and 6 hours after the transition), carries a weight of 5/24, and the third, fourth and fifth assessments, collected after 12 hours, 18 hours and 24 hours of the transition, respectively, will each carry a weight of 6/24.

The secondary objectives are to estimate the association between the rate of adherence to low V_T_ ventilation in spontaneous ventilation and survival, estimate the incidence of asynchrony in the first 24 hours after the transition to spontaneous ventilation and associated mortality, estimate the proportion of patients who returned to sedation and controlled MV in the first 24 hours or at any time after the transition to spontaneous ventilation, assess the adherence to low positive end-expiratory pressure (PEEP) by fraction of inspired oxygen (FiO_2_) table in the first 24 hours after the transition to spontaneous ventilation, and identify barriers associated with nonadherence to low V_T_ ventilation during spontaneous ventilation.

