The comparison of V_T_ during the initial 24 hours of spontaneous ventilation (less than 8mL/kg of PBW versus greater than 8mL/kg) in relation to ventilator-free days within 28 days will be performed using mixed generalized regression models considering the distribution that best fits the data, incorporating center as a random effect. We constructed a conceptual causal diagram in the format of a directed acyclic graph (DAG),^(24)^ including the association between V_T_ during the first 24 hours of spontaneous ventilation and ventilator-free days at 28 days and the most relevant variables (Figure 1S - Supplementary Material): body mass index (BMI) and SAPS 3 at baseline, SOFA on the day before transition, PaO_2_/FiO_2_ at the moment of the ARF diagnosis, and PEEP, RASS, and pH one hour before transition.

All analyses will be performed using the R statistical program (R Core Team; Vienna, Austria; https://www.R-project.org), and we will consider p < 0.05 to indicate statistical significance.

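### Ventilator-free days are counted from inclusion while the VT group is set by readings over the next 24 hours, so the patient's course in that window can bias the primary association in either direction

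*Protocol article*

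**What the plan says.** - **Outcome clock** (Follow-up): "Ventilator-free days will be calculated as the number of days alive and out of MV to day 28". A death earlier than that scores zero. The starting point is fixed as well: "the day of inclusion will be considered day 0".
- **Entry** (Data collection on the day of transition to spontaneous ventilation): "We will include patients who are transitioned and remain for at least one hour in one of the following ventilatory modes".
- **Exposure** (Objectives and outcomes): "Tidal volume will be assessed five times over the first 24 hours after the transition to spontaneous ventilation". To place a patient below or above 8 mL/kg, "we will calculate the weighted average V_T_ based on the duration of each evaluation period". The 1-hour reading weighs 1/24 and the 6-hour reading 5/24; the remaining three are "collected after 12 hours, 18 hours and 24 hours of the transition, respectively, will each carry a weight of 6/24".
- **Leaving the mode**: return to sedation and controlled ventilation within the first 24 hours is itself a listed outcome, so the protocol expects some patients to leave during the exposure window.
- **Model** (Statistical plan analysis): a mixed generalized regression of ventilator-free days on VT group, with center as a random effect. The causal diagram lists BMI and SAPS 3 at baseline, SOFA on the day before transition, PaO2/FiO2 at diagnosis, and "PEEP, RASS, and pH one hour before transition".
- **Survival**: Cox and Kaplan-Meier by 24-hour VT, with no time origin given.

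**The concern.** A patient can enter one hour after transition, and from then on the outcome clock runs. The group is known only at 24 hours. Two things can happen in between.

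1. Extubation, death or return to controlled ventilation ends the exposure readings and at the same time determines much of the outcome.
2. VT itself can respond to the patient's course. The Discussion says that VT in this phase depends on the level of assistance and on the patient's effort. Both can change as a patient weans or deteriorates, so VT at 6 to 24 hours may partly record progress toward extubation, which is what ventilator-free days measure.

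Every listed variable is measured at baseline or before transition, so none can adjust for events inside the window. The limitations paragraph mentions that 24 hours may not represent later days and that VT is not continuous, but not this overlap. At stake is a primary objective: the VT/ventilator-free-days association could partly reflect the patient's course rather than VT.

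**Working it through.** **1. The plan's own figures reproduce.** Inputs from Sample size calculation: prevalence 50%, precision 5%, loss 10%, difference 3 days, SD 9 days. Two-sided 5% is assumed.

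- N = 1.96² × 0.25 / 0.05² = 384.1; × 1.10 = 422.6, against the stated 422.
- After 10% loss: 422 × 0.9 = 379.8 patients.
- 25/75 split: SE = 9 × √(1/94.95 + 1/284.85) = 1.07; 3/1.07 − 1.96 = 0.85; power 80.3%.
- 50/50 split: SE = 9 × √(4/379.8) = 0.92; power 90.1%.

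**2. Share of the exposure measured after the clock can start.** 5/24 + 3 × 6/24 = 23/24.

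**3. Size under a true null.** The documents give no rate of leaving the mode early and no figure for how VT changes before extubation, so these inputs are assumptions: VT mean 8 mL/kg (SD about 1.8), 20% with zero ventilator-free days, 15% or 25% of the rest extubated by 24 hours, and VT shifted from the 6-hour reading onward in patients extubated within 48 hours. VT has no effect on outcome, and the weights are rescaled to the readings available.

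| Assumed VT shift before extubation | Spurious difference in days, low minus high VT (15% / 25% extubated) |
|---|---|
| none | 0 / 0 |
| 0.5 mL/kg lower | +0.72 / +0.90 |
| 1.0 mL/kg lower | +1.40 / +1.73 |
| 0.5 mL/kg higher | −0.69 / −0.93 |
| 1.0 mL/kg higher | −1.43 / −1.74 |

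Varying the remaining settings widens this to roughly 0.7 to 1.9 days either way. Against the 3-day target, 0.7/3 = 23% and 1.9/3 = 63%. A VT rise of 0.5 mL/kg confined to the zero-day patients gives about +1.6 days.

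**4. Leaving the mode alone, with VT unrelated to prognosis.** Assumptions here: extubated within 24 hours 0 to 25%, returned to controlled ventilation 5 to 20%, died 1 to 2%. With available readings rescaled, last value carried forward, or complete readings only, the difference is −0.08 to +0.07 days, that is, none. If readings after return to controlled ventilation were counted at an assumed 6.5 mL/kg, it is −0.6 to −1.3 days.

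**5. What the sensitivity analyses would do.**

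- *1-hour VT*: bias within 0.05 days of zero in every run. This is built in, because VT was allowed to change only from 6 hours.
- *24-hour landmark* (patients still ventilated at 24 hours): with a VT fall before extubation, +0.47 to +0.72 days (0.5 mL/kg) and +0.95 to +1.33 (1.0 mL/kg) remain. As shares, 0.47/0.72 = 65% and 0.72/0.90 = 80%; 0.95/1.40 = 68% and 1.33/1.73 = 77%. It gives no reduction when VT rises in failing patients.
- *Landmark power*, 10% excluded: 379.8 × 0.9 = 341.8 patients; at 25/75, SE = 9 × √(1/85.46 + 1/256.37) = 1.12; 3/1.12 − 1.96 = 0.71; power 76.1%. At 50/50 it is 86.9%. With 20% excluded, 71.1% and 82.8%.

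**The case against.** The strongest reply has five parts.

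- **Direction.** A reader might infer that the plan makes low VT look beneficial. The documents do not support that. They say that VT varies with assistance and effort, not that it falls before extubation. Reversing the assumed shift reverses the sign, and with no shift the bias is zero. This part stands in full.
- **Survival.** A reader might take survival, too, to be counted from inclusion. The day-0 rule sits inside the definition of ventilator-free days. For the Cox and Kaplan-Meier analysis, inclusion is only the likely origin. This stands.
- **Early leavers.** How to treat readings after a patient leaves the mode is detail that a condensed article may leave to a fuller plan, so its absence is not held against the study. This stands. The overlap itself is different: the article fixes the exposure window, day 0 and the listed variables.
- **Remedies.** The landmark leaves most of the weaning-driven bias, because moving the clock does not undo VT responding to imminent extubation. The 1-hour VT is noisier, carries 1/24 of the intended exposure, and is still open to confounding: in a separate null simulation, a correlation of 0.3 between a patient's VT level and recovery gave about 2.2 days in either direction. The 24-hour average was chosen deliberately as more representative. All this stands, and it is why both belong as sensitivity analyses and not as replacements or as a test that the main result must pass.
- **Observational wording.** The study claims association only. That softens the point but does not remove it: the article builds a causal diagram for this comparison and hopes to inform practice.

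**Conclusion.** The concern holds as a structural overlap: the outcome clock can start after one hour, 23/24 of the exposure weight is measured later, and the listed variables all precede the window. Following the plan as written can bias a primary association.

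The size is not known from the documents. Under assumed VT shifts of 0.5 to 1 mL/kg tied to the patient's course, it is roughly 0.7 to 1.9 days, about a quarter to nearly two thirds of the 3-day target, and the sign depends on how VT relates to recovery or deterioration. It is zero if VT is unrelated to the patient's course and only the available spontaneous-mode readings are used. No claim that low VT will be favoured, and no claim about the survival analysis beyond its unstated origin, follows from the text. The change is worth making because the association is a primary objective and the remedy is cheap.

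**What to change.** Keep the 24-hour weighted average for the prevalence estimate and as the stated exposure. Add to the analysis plan:

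1. A sensitivity analysis with the 1-hour VT as exposure. Every included patient should have this reading, and it largely precedes later weaning changes.
2. A sensitivity analysis from a 24-hour landmark, in patients alive and still in spontaneous ventilation at 24 hours, with ventilator-free days and survival counted from that point.
3. The time origin for the Cox and Kaplan-Meier analysis.
4. A sentence that the conclusion on VT and ventilator-free days will be worded cautiously if these analyses differ from the main one, and a mention of the overlap among the limitations.

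The cost is wording and the extra model runs, on readings the protocol already collects. The limits should be stated with the results: the 1-hour value is noisier and still open to confounding; the landmark removes only part of the bias from VT responding to weaning, drops early leavers, and lowers power from 80.3% to 76.1% at a 25/75 split if 10% are excluded. Restoring that power would take about 422/0.9 = 469 inclusions, which a sensitivity analysis does not require.

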**Results::**

We plan to include 422 patients in ten countries. The primary outcomes are the prevalence of low tidal volume in the first 24 hours of spontaneous ventilation and ventilator-free days on day 28. The secondary outcomes are intensive care unit and hospital mortality, incidence of asynchrony and return to controlled ventilation and sedation.

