### Sample size calculation

There are no previous studies that have estimated the rate of adherence to low V_T_ in patients with spontaneous ventilation; therefore, we used a conservative approach. To estimate the prevalence with a confidence limit of 5% precision, an anticipated adherence of 50%, and up to 10% loss to follow-up, we estimated that we need to include 422 patients. Additionally, we calculated the power to detect a 3 day difference in ventilator-free days with a standard deviation of 9 days,^(22)^ and we anticipate a statistical power of at least 80% even with a loss to follow-up rate of 10%, provided that the prevalence is between 25 and 75%.

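### The reintubation rule for ventilator-free days can score a survivor still ventilated at day 28 above an otherwise identical patient who was freed again

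*Protocol article*

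**What the plan says.** The abstract of the protocol article names this endpoint among the primary outcomes: "The primary outcomes are the prevalence of low tidal volume in the first 24 hours of spontaneous ventilation and ventilator-free days on day 28". The Objectives and outcomes section makes the relation between low tidal volume and this endpoint a primary objective ("its association with ventilator-free days on day 28").

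The Follow-up section gives the scoring:

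- General definition: "Ventilator-free days will be calculated as the number of days alive and out of MV to day 28".
- Time origin: "the day of inclusion will be considered day 0".
- The only rule that sets the score to zero: "Patients who die before day 28 will be considered to have zero ventilator-free days".
- A special rule "for patients who are extubated and reintubated in the first 28 days", under which the score is the number of "days alive and out of MV from the day of the last successful extubation (> 48 hours without MV) to day 28".

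Tracheostomized patients have their own clause and are outside this point.

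**The concern.** The parenthesis in the reintubation rule is the only definition of a successful extubation, and it looks no further than 48 hours. Suppose a patient is reintubated after more than 48 hours and is alive on the ventilator at day 28. The last extubation that meets the definition is the earlier one, so the days that followed it are credited. If the same patient is extubated again and stays off, the start of counting moves to the later extubation and the earlier days drop out. The additional success can lower the score.

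The endpoint is read as higher is better. A rule that can place the better course below the worse one adds error to a comparison of means and to a rank comparison. If such patients are unevenly spread over the two VT groups, it also biases the primary association.

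**Working it through.** **The plan's own figures, for scale.** Inputs from Sample size calculation: "confidence limit of 5% precision, an anticipated adherence of 50%, and up to 10% loss to follow-up", and a 3-day difference with standard deviation 9. The precision formula gives n = 1.96² × 0.5 × 0.5 / 0.05² = 384.1, and 384 × 1.10 = 422.4, which reproduces the stated 422. With 379 to 380 patients after 10% loss and a two-sided 0.05 test (sidedness assumed), power for 3 days is 80.2 to 80.3% at a prevalence of 25% or 75%, and 90% at 50%. These figures reproduce and are not in dispute. The 3-day difference is the yardstick below.

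**Scoring two histories.** Let e be the first extubation day, r the reintubation day and f the final extubation day. Both off-MV intervals last more than 48 hours. Patient A is still ventilated at day 28. Patient B has the same course up to day f and then stays off MV.

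Reading 1 counts only days actually off MV from the last qualifying extubation:

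- A = r − e
- B = 28 − f

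Reading 2 counts calendar days from the last qualifying extubation to day 28:

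- A = 28 − e
- B = 28 − f

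The general definition counts all days off MV:

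- A = r − e
- B = (r − e) + (28 − f)

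| e, r, f | A, reading 1 | A, reading 2 | B, both readings | A, general | B, general |
|---|---|---|---|---|---|
| 3, 20, 24 | 17 | 25 | 4 | 17 | 21 |
| 5, 10, 25 | 5 | 23 | 3 | 5 | 8 |
| 3, 8, 12 | 5 | 25 | 16 | 5 | 21 |

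**When the order reverses.** On reading 1, A exceeds B when r − e > 28 − f, that is, when the first off-MV interval is longer than the final one. The third row shows the right order (5 against 16). Listing all whole-day histories with a first interval of at least 3 days and f no later than day 25, the order reverses in 825 of 1,771, or 47%. This is an unweighted count of possible histories, not a frequency of patients. On reading 2, A always exceeds B, because e is earlier than f.

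**Conflict inside the section.** On reading 1 the reintubation rule agrees with the general definition for A (17 and 17) but not for B (4 and 21). On reading 2 it also departs from the general definition for A (25 and 17), since it credits days spent on the ventilator.

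**Size, by assumption.** The documents give no frequency for A-type patients. Measured against a rule that scores them zero, a group's mean rises by share × credited days. With about 10 credited days, a share of 1% gives 0.01 × 10 = 0.1 day and a share of 5% gives 0.05 × 10 = 0.5 day. The shift in the between-group difference, at equal credit, is the difference in shares × credit:

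- 1 percentage point × 3 days = 0.03 day
- 5 points × 10 days = 0.5 day, one sixth of the 3-day target
- 10 points × 15 days = 1.5 days
- 10 points × 23 days = 2.3 days (reading 2 only, for an extubation on day 5)

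With equal shares and equal credit in both groups, the shift is zero.

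**The case against.** The strongest reply is that A's score is not wrong. A was alive and off the ventilator for 17 days, and the general definition gives 17. The patient out of line is B, whose earlier free days are discarded. That stands: the fault lies in mixing two counting principles, and A's credit is an error only if freedom from MV at day 28 is the intended requirement.

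A reader might infer more than the text supports:

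- *That a patient never freed can outscore one who was.* The rule credits nothing for an extubation of 48 hours or less, so A must have had a real spell off MV. The accurate description is a patient not free of MV at day 28.
- *That the rule reverses the order of late reintubations in general.* On reading 1 it does so only when the first interval is longer than the final one.
- *That the primary association is biased.* This needs the share or the credited days to differ by VT group, and the documents give no evidence that they do.
- *That scoring A as zero is the only repair.* Zero puts A level with a patient who died and moves away from the general definition. Counting all off-MV days also removes the reversal.

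The group is also narrow: extubated for more than 48 hours, reintubated, alive, still ventilated at day 28 and not tracheostomized. What the reply does not remove is that the explicit rule can rank B below A although B has every free day that A has and more. Because the rule is stated, an analysis plan that follows it inherits the problem.

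**Conclusion.** The point holds as an internal inconsistency in the scoring of a primary outcome. No reading of the reintubation rule avoids it, and nothing elsewhere in the article repairs it. For an individual patient the effect can be large: 17 against 4 days on reading 1, where the general definition gives 17 against 21.

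For the trial it is probably small, though that is a judgement because no frequency is given. Under the assumptions shown, one group's mean rises by 0.1 to 0.5 day, and the between-group difference moves by 0.03 to 2.3 days. The top of that range needs both a 10-point imbalance and the calendar reading. Without an imbalance by VT group in share or credited days, the rule adds noise and not bias. The sample size and power calculations are unaffected. The rule should be corrected because this is a primary outcome and the correction is cheap.

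**What to change.** Choose one counting principle and record the choice, with its date, before ventilator-free days are derived. Either of these is consistent:

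1. **Keep the last-successful-extubation approach.** For reintubated patients, count from the last extubation that lasted more than 48 hours and after which the patient stayed off MV to day 28, and score a patient on MV at day 28 as zero. In the first example A scores 0 and B scores 4. For an extubation in the last two days, the 48 hours run past day 28; follow-up to hospital discharge or death allows that check.
2. **Count all days alive and off MV to day 28**, as the general definition says, with zero for death before day 28. A scores 17 and B scores 21. The text should then say whether off-MV spells of 48 hours or less count.

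Make one of them primary, report the other as a sensitivity analysis, and bring the general definition and the reintubation clause into line.

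The cost is a sentence in the outcome definition, a change to the derivation code and one more analysis. The extubation and reintubation dates are already needed for the current rule. A few patients change score: under option 1 some fall to zero, and under option 2 those freed a second time regain their earlier days. Recruitment started in June 2023, so this changes the scoring of a primary outcome in a study already under way. It should be documented as such and settled without reference to results by VT group.
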